### Sample size considerations

As per details provided in the 'Feasibility counts' section, if we assume a 0.5% prevalence of intellectual disabilities as per findings reported by Glover et al. (2019; 2020) using a CPRD GOLD database with a follow-up period of April 2010-March 2014, then within the population of currently registered research acceptable (de-duplicated) patients (N=16,305,791 in total; N=3,020,680 for GOLD database and N=13,285,111 for Aurum database) 81,529 patients would be expected to have intellectual disabilities on any given day. Prevalence studies of challenging behaviours in nationwide primary care samples are lacking, but if we assume that a prevalence of challenging behaviours in a population of people of all ages with intellectual disabilities in England is as described in a study of seven District Health Authorities in the UK by Emerson et al. (2001), 16.5% (N=13,452) of patients with intellectual disabilities are expected to have any form of challenging behaviours on any given day during the study follow-up period of 2009-2019, with prevalence rates for specific types of challenging behaviours expected to be much higher (e.g., 42.0% for aggressive behaviours). Given the estimated sample size, the study is expected to have sufficient statistical power. References after amendments: Emerson, E., Kiernan, C., Alborz, A., Reeves, D., Mason, H., Swarbrick, R., Mason, L., & Hatton, C. (2001). The prevalence of challenging behaviours: A total population study. *Research in Developmental Disabilities*, 22(1), 77-93.

## **Planned use of linked data and benefit to patients in England and Wales**

Our analysis will use the Clinical Practice Research Datalink (CPRD) GOLD and Aurum databases which will be anonymised. Patients' GP records will be linked with:

1. HES Admitted Patient Care to test for interaction effects with the effect modifier of physical conditions;
2. Mental Health Services Data Set (MHSDS), available for the period of April 2007-November 2015, to assess any attenuation in the associations between the mental comorbidities moderator and challenging behaviours;
3. Practice and Patient Level Index of Multiple Deprivation to adjust for confounding effects of socioeconomic deprivation for all analyses.

**Importance/impact:** This project will extend the existing work on challenging behaviours in people with intellectual disabilities by using nationwide CPRD data to investigate the incidence of challenging behaviours in a large nationwide population of primary care patients with intellectual disabilities in England. Using stratified Cox proportional hazard models, we will also examine the association between challenging behaviours and physical conditions (i.e. pain, sleep problems, constipation, epilepsy, urinary/bowel incontinence and sensory impairments) in this population, including exploring how different health (e.g. severity of intellectual disabilities, co-occurring autism/genetic syndromes/mental comorbidities), demographic (e.g. age, gender, ethnicity) and socioeconomic (e.g. Practice/Patient Level Index of Multiple Deprivation) factors may affect this relationship. The proposed study will provide a much-needed foundation for future research and intervention development designed to reduce health inequalities experienced by patients with intellectual disabilities through better management of challenging behaviours and improved understanding of their association with physical health problems in this population. This is particularly important in the light of lack of existing evidence in this area of research.

**Dissemination:** We will adopt a diverse strategy for dissemination to ensure that study outputs are useful, timely, appropriate and action oriented. These will include reports targeted at particular audiences (e.g. individuals and families affected by intellectual disabilities and challenging behaviours, health and social care practitioners and commissioners, policy makers and academics). We will publish in peer reviewed scientific journals and disseminate findings via the University of Glasgow, Warwick, Central Lancashire and St George's, University of London websites, newsletters and social media channels.

Study results will also be presented and discussed with NHS Education England and Scotland, Health Education and Improvement Wales, Departments of Health and Social Care in England and Wales, Wales Challenging Behaviour Community of Practice, Healthcare Improvement Scotland, Scottish Government's Mental Health Directorate and Cross-Party Disability Group and at conferences relevant to frontline clinicians (i.e. Royal Colleges of Psychiatrists and General Practitioners and Public Health England conferences). We will also disseminate findings to the authors of the NICE guideline NG11 'Challenging behaviour and learning disabilities: prevention and interventions for people with learning disabilities whose behaviour challenges', the British Psychological Society's Clinical Practice Guidelines 'Psychological interventions for severely challenging behaviours shown by people with learning disabilities' and the Welsh Government's Learning Disability Improving Lives Programme.

## Definition of the study population

Data on all patients with intellectual disabilities will be acquired from CPRD. Individuals with intellectual disabilities will be identified using Read codes in Appendix 1. Co-occurring challenging behaviours will be defined as a binary variable (present or not) based on READ codes in Appendix 1. Patients registered in a practice between January 1 January 2009 and 31st December 2019 will be included in the study. We require that their practice allows linkage to HES, MHSDS and IMD data, resulting in the inclusion of English practices. Patients who are registered at CPRD practices not participating in the linkage scheme, or who have individually opted out, will not be included.

Earliest cohort entry date will be 1/1/2009. Patients who register after 1/1/2009, or who are diagnosed with intellectual disabilities during the study period, will be followed from that date. Patients will be censored if they transfer out from their CPRD practices, or opt out before the end of the study period (31/12/2019). However, challenging behaviour diagnoses of patients who leave a CPRD practice prior to the end of the study period will be included in a sensitivity analysis.

Index case for a case would be one of the following:

- 1/1/2009 (if a patient is actively registered on this date with a diagnosis of challenging behaviours prior to 2009)
- date of diagnosis (if a patient's date of first diagnosis of challenging behaviours is after 1/1/2009 while they are registered)
- date of registration (if a patient's date of registration is after 1/1/2009 and they have a prior diagnosis to that registration)

Inclusion criteria:

- all patients with intellectual disabilities (as defined in READ codes in Appendix 1) registered at a general practice for at least six months prior to cohort entry date
- patients who receive a diagnosis of intellectual disabilities after cohort entry date and have a valid registration status for at least six months

Exclusion criteria

- patients registered at practices not participating in the linkage scheme, or who have individually opted out

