## **Objectives, specific aims & rationale**

The aim of this project will be firstly to investigate longitudinal trends in the incidence of challenging behaviours in a nationwide population of primary care patients with intellectual disabilities, using data from the Clinical Practice Research Datalink. We will also investigate if there is an association between physical conditions and challenging behaviours in patients with intellectual disabilities and what the nature and direction of this association may be.

The project aims to answer the following research questions:

1. What is the 1-, 5- and 10-year incidence of challenging behaviours in a nationwide population of primary care patients with intellectual disabilities?
2. Do physical conditions (i.e. pain, sleep problems, constipation, epilepsy, urinary/bowel incontinence and sensory impairments) increase/decrease the incidence of challenging behaviours in primary care patients with intellectual disabilities?
3. To what extent do health factors (i.e. severity of intellectual disabilities, co-occurring autism/genetic syndromes/mental comorbidities) affect the incidence of challenging behaviours in primary care patients with intellectual disabilities?
4. Is the relationship between the presence of physical conditions and challenging behaviours in patients with intellectual disabilities accounted for by demographic (e.g. age, gender, ethnicity) and socioeconomic (e.g. Practice/Patient Level Index of Multiple Deprivation) factors?

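### Patients with a challenging-behaviour diagnosis before cohort entry are treated as cases dated at entry, and nothing keeps them out of the incidence and first-event Cox analyses

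*Protocol*

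**What the plan says.** *Definition of the study population* in the Protocol lists three index dates for a case:

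- First bullet: "1/1/2009 (if a patient is actively registered on this date with a diagnosis of challenging behaviours prior to 2009".
- Second bullet: "date of diagnosis (if a patient's date of first diagnosis of challenging behaviours is after 1/1/2009 while they are registered".
- Third bullet: "date of registration (if a patient's date of registration is after 1/1/2009 and they have a prior diagnosis to that registration".

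The same section sets the start of follow-up: "Earliest cohort entry date will be 1/1/2009", with later registrants and patients diagnosed later with intellectual disabilities followed from that later date. The only exclusion is "patients registered at practices not participating in the linkage scheme, or who have individually opted out". The inclusion rule requires patients to be "registered at a general practice for at least six months prior to cohort entry date", but does not require them to be free of the outcome during that time.

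Research question 1 (*Objectives, specific aims & rationale*) asks: "What is the 1-, 5- and 10-year incidence of challenging behaviours in a nationwide population of primary care patients with intellectual disabilities". Question 2 asks whether physical conditions raise or lower that incidence. Phase 1 of *Data/statistical analysis* bases the incidence on a binary outcome, a relevant Read code on record, and does not limit it to a first code or a code after entry. Phase 2 makes stratified Cox models the main analysis and adds a Poisson regression for patients with multiple events.

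**The concern.** The first and third bullets apply only to patients whose challenging behaviour was recorded before follow-up began. The Protocol calls them cases and dates them at entry. Incidence and a first-event Cox model both need patients who are free of the outcome at time zero, and no step in the Protocol secures this.

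Two results are at stake. The incidence figures for question 1 would sit on a floor equal to the coded prevalence at entry, whatever the true onset rate. The hazard ratios for question 2 could mix two associations: that of physical conditions with existing behaviour and that with new onset. *Exposures, outcomes and covariates* identifies physical conditions by any relevant Read code, without a timing rule. For a prevalent case the condition may therefore have followed the behaviour, and the study aims to describe the direction of the association.

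**Working it through.** **Inputs from the Protocol**

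- Registered patients: 3,020,680 (GOLD) + 13,285,111 (Aurum) = 16,305,791 (*Sample size considerations*).
- Prevalence of intellectual disabilities: 0.5% (same section).
- Prevalence of challenging behaviours: 16.5%, stated as 13,452 patients (same section); range across large population studies 4-22% (*Study background*).
- Incidence rate: none given. A rate of 1-3% per year among those at risk is an assumption.

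**Reproducing the Protocol's figures**

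16,305,791 × 0.005 = 81,528.96, stated as 81,529. Then 81,529 × 0.165 = 13,452.3, stated as 13,452. Both reproduce. Without the prevalent cases, 81,529 − 13,452 = 68,077 remain at risk.

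**Cumulative incidence**

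For rate r, time t and prevalence at entry p:

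- Among those free of the outcome at entry: 1 − exp(−rt).
- With prevalent cases counted over the whole cohort: p + (1 − p)(1 − exp(−rt)).

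Example with p = 0.165, r = 0.02 and t = 10: 1 − exp(−0.2) = 18.1%, and 0.165 + 0.835 × 0.1813 = 31.6%.

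Each cell shows the correct percentage, the counted percentage and their ratio.

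| p | r per year | 1 year | 5 years | 10 years |
|---|---|---|---|---|
| 4% | 1% | 1.0 → 5.0 (5.0) | 4.9 → 8.7 (1.8) | 9.5 → 13.1 (1.4) |
| 4% | 2% | 2.0 → 5.9 (3.0) | 9.5 → 13.1 (1.4) | 18.1 → 21.4 (1.2) |
| 4% | 3% | 3.0 → 6.8 (2.3) | 13.9 → 17.4 (1.2) | 25.9 → 28.9 (1.1) |
| 16.5% | 1% | 1.0 → 17.3 (17.4) | 4.9 → 20.6 (4.2) | 9.5 → 24.4 (2.6) |
| 16.5% | 2% | 2.0 → 18.2 (9.2) | 9.5 → 24.4 (2.6) | 18.1 → 31.6 (1.7) |
| 16.5% | 3% | 3.0 → 19.0 (6.4) | 13.9 → 28.1 (2.0) | 25.9 → 38.1 (1.5) |
| 22% | 1% | 1.0 → 22.8 (22.9) | 4.9 → 25.8 (5.3) | 9.5 → 29.4 (3.1) |
| 22% | 2% | 2.0 → 23.5 (11.9) | 9.5 → 29.4 (3.1) | 18.1 → 36.1 (2.0) |
| 22% | 3% | 3.0 → 24.3 (8.2) | 13.9 → 32.9 (2.4) | 25.9 → 42.2 (1.6) |

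The prevalent share of counted cases is p divided by the counted figure. At 16.5% and 1 year it is 16.5/17.3 to 16.5/19.0, or 95% to 87%. At 10 years it is 16.5/31.6 = 52% for 2% per year and 16.5/38.1 = 43% for 3% per year.

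**Cox hazard ratio**

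A simulation used 20,000 patients per scenario, one run each. It assumed 30% exposed, 2% per year incidence, 16.5% prevalent at entry and censoring spread evenly over 11 years. Prevalent cases were kept as events on day 1 and made up 62-66% of all events.

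| True hazard ratio | Odds ratio with prevalent behaviour | Estimate, prevalent cases kept | Estimate, prevalent cases removed |
|---|---|---|---|
| 1.0 | 1.0 | 1.00 | 1.05 |
| 1.0 | 1.5 | 1.21 | 0.93 |
| 1.0 | 3.0 | 1.84 | 0.93 |
| 1.5 | 1.0 | 1.13 | 1.45 |
| 1.5 | 1.5 | 1.50 | 1.67 |
| 1.5 | 3.0 | 1.97 | 1.46 |

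The last column shows the noise of single runs: 0.93-1.05 around 1.0 and 1.45-1.67 around 1.5. With prevalent cases kept, the estimate is pulled towards the association with prevalent behaviour. It stays near the truth when the two associations are alike.

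**The case against.** The Protocol nowhere says outright that previously diagnosed patients go into the incidence numerator or the Cox event count. The three bullets could be read as dating case status only, leaving prevalent and new cases to be separated later. This objection has weight: counting them is a strong inference, not an explicit statement. It does not dispose of the point, because the text calls these patients cases, dates them at entry, excludes none of them and sets no time limit on the outcome. Nor is this a detail left open for an analysis plan. The Protocol states a rule, which a later plan would have to override.

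Some stronger readings are tempting, but the document does not support them:

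- *New cases have no time at risk.* A reader might infer this from the second bullet. But the same section starts follow-up at entry, so a new case contributes time from entry to diagnosis, and the diagnosis date serves as the event date.
- *These are case-control index rules.* The Protocol states a retrospective cohort and says comparison groups do not apply. Where the rules came from is conjecture.
- *The Cox results are bound to be wrong.* Some survival software drops records with zero follow-up. That would remove these patients, although silently. If they are kept, bias arises only when the two associations differ.
- *The incidence would be mostly prevalence at every horizon.* At 16.5% this is so at 1 year, but prevalent cases are only about half or fewer of the 10-year total at 2-3% per year.

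Two further objections stand. The 16.5% is a population prevalence, and *Limitations of study design* expects under-recording, so the share coded before entry may be lower. Previously diagnosed patients may also legitimately contribute to the multiple-event Poisson analysis, so their presence in the cohort is not in itself an error.

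**Conclusion.** The point holds for the first and third bullets. Followed as written, they put prevalent cases into the 1-, 5- and 10-year incidence and allow them into the Cox models as time-zero events.

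The effect on incidence is largest at 1 year and shrinks with longer follow-up. Across the assumed 1-3% per year and the Protocol's 4-22% prevalence, the inflation runs from 2.3- to 23-fold at 1 year and from 1.1- to 3.1-fold at 10 years. These sizes rest on the assumed rate, and on coded prevalence at entry being close to the population figures. The effect on the hazard ratios depends on how time-zero records are handled and on how far the association with existing behaviour differs from that with new onset.

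Questions 1 and 2 both depend on this rule, so it should be corrected before the cohort is built.

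**What to change.** Keep the second bullet, the date of first diagnosis, as the event date. Replace the first and third bullets with wording such as:

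> *Patients with any challenging-behaviour code on or before cohort entry are excluded from the incidence and first-event Cox analyses and reported separately as baseline prevalence. For all others, time at risk runs from cohort entry to the first challenging-behaviour code after entry or censoring.*

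Previously diagnosed patients may stay in the multiple-event Poisson analysis if they are identified as such.

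The cost is a change of wording, one more step in building the cohort and fewer cases in the Cox models. At 16.5% prevalence, about 68,077 of 81,529 patients would remain at risk. No new data are needed.

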### **Phase 1**

We will calculate the incidence of challenging behaviours within the group with intellectual disabilities. Our binary outcome will be defined on the basis of having a record of a relevant Read code for co-occurring challenging behaviours (Appendix 1). Records will be stratified by age, sex, severity of intellectual disabilities and/or co-occurring physical conditions/autism/genetic syndromes/mental comorbidities if cell sizes allow. Tables of baseline characteristics will be described for all patients with intellectual disabilities. For continuous data, mean, median, range, and standard deviations will be calculated. For categorical variables, frequency and percentages will be reported.

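### For patients first coded with intellectual disability during the study, the second case index rule can place a case before follow-up starts, and the entry date itself is stated inconsistently

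*Protocol*

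**What the plan says.** All the rules at issue stand in the protocol section Definition of the study population.

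- **Start of follow-up.** "Earliest cohort entry date will be 1/1/2009". Patients "who are diagnosed with intellectual disabilities during the study period, will be followed from that date".
- **Index for a case, rule 1.** "1/1/2009 (if a patient is actively registered on this date with a diagnosis of challenging behaviours prior to 2009".
- **Rule 2.** "date of diagnosis (if a patient's date of first diagnosis of challenging behaviours is after 1/1/2009 while they are registered".
- **Rule 3.** "date of registration (if a patient's date of registration is after 1/1/2009 and they have a prior diagnosis to that registration".
- **Second inclusion criterion.** "patients who receive a diagnosis of intellectual disabilities after cohort entry date and have a valid registration status for at least six months".

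The only exclusion concerns non-linked practices and opt-outs. An earlier challenging-behaviour code is not an exclusion. The Phase 1 section adds: "Our binary outcome will be defined on the basis of having a record of a relevant Read code for co-occurring challenging behaviours". It puts no condition on when that record was made.

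**The concern.** A patient can come under observation at one of three dates: 1/1/2009, a later registration, or an in-study diagnosis of intellectual disability. Rules 1 and 3 deal with challenging behaviour recorded before the first two by moving the index to that date. No rule does this for the third. Rule 2 picks up these patients and leaves the index at the behaviour code, which may precede the diagnosis that starts their follow-up.

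The first research question asks for the 1-, 5- and 10-year incidence. An event that precedes entry belongs to time that is not in the denominator, so counting it raises the estimate. The second inclusion criterion makes matters worse, because it places the diagnosis later than cohort entry although the follow-up rule makes that diagnosis the entry. If entry is taken as 1/1/2009 or registration instead, the years before the diagnosis become person-time that only patients who stay until they are diagnosed can contribute.

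**Working it through.** **The protocol's own figures.** 16,305,791 × 0.005 = 81,528.96, stated as 81,529. 81,529 × 0.165 = 13,452.3, stated as 13,452. Both reproduce, and neither bears on this point.

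**The rules applied to three records, all registered since 2005**

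| Record | Disability coded | Behaviour first coded | Follow-up starts | Index (rule 2) | Index minus start |
|---|---|---|---|---|---|
| A | before 2009 | 2012 | 1/1/2009 | 2012 | +3 years |
| B | 2015 | 2017 | 2015 | 2017 | +2 years |
| C | 2015 | 2012 | 2015 | 2012 | −3 years |

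Record C meets rule 2 and the Phase 1 outcome definition, and no exclusion removes it. If the second inclusion criterion is read as putting entry at 1/1/2009, record C's index is at +3 years. But then record B brings in six years (2009 to 2015) during which it could not have left unobserved and still been in the cohort.

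**Illustrative size.** From the documents: window T = 11 years (1/1/2009 to 31/12/2019). Assumed, because the documents do not give them: behaviour rate after the disability code λ = 0.02 per year; rate before it kλ; leaving rate μ = 0.06 per year; share s of registered patients whose first disability code falls in the study, with code dates u spread evenly over 0 to T.

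- Person-years per patient coded before the study: E = (1 − e^(−(λ+μ)T)) / (λ+μ) = 7.315.
- Pre-entry events per in-study-coded patient: A = (1/T) ∫ e^(−μu) (1 − e^(−kλu)) du.
- Person-years per in-study-coded patient, counting only those free of the behaviour at entry: B = (1/T) ∫ e^(−(μ+kλ)u) (1 − e^(−(λ+μ)(T−u))) / (λ+μ) du.
- Literal rate ÷ correct rate = 1 + sA / (λ[(1−s)E + sB]).

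Example with k = 1 and s = 0.20: A = 0.0670, B = 3.128. Person-years = 0.8 × 7.315 + 0.2 × 3.128 = 6.478. Events after entry = 0.02 × 6.478 = 0.1296. Events before entry = 0.2 × 0.0670 = 0.0134. Ratio = 1 + 0.0134 / 0.1296 = 1.10.

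| Rate before the code | A | B | s = 10% | s = 20% | s = 30% |
|---|---|---|---|---|---|
| half (k = 0.5) | 0.0347 | 3.237 | +2.5% | +5% | +8.5% |
| equal (k = 1) | 0.0670 | 3.128 | +5% | +10% | +17% |
| double (k = 2) | 0.1256 | 2.927 | +9% | +19.5% | +31% |

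Simulation under the same assumptions agrees to about one percentage point.

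**Sensitivity to the assumed rate.** In a simulation with no leavers, k = 1 and s = 20%, the ratio was 1.114, 1.116 and 1.118 at 10, 20 and 30 per 1,000 person-years. The assumed behaviour rate therefore matters little; the share s and the factor k drive the result. Counting only first codes after entry recovered the assumed rate each time.

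These figures are for the rate over the whole window, not for each of the three horizons.

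**The case against.** The strongest reply is that the protocol never says the index date is the event date in the incidence numerator. It lists dates that define the index for a case and says elsewhere that patients are followed from the diagnosis. An analyst could reasonably count only events within follow-up, and record C would then not be counted. That stands as far as it goes: the text permits the error and does not order it. It does not remove the conflict. Rules 1 and 3 keep patients with earlier codes as cases, and the Phase 1 outcome has no timing condition, so the text does not point to the safe reading either.

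It can also be said that the two readings of the entry date exclude each other, so that under the earlier entry date the negative time disappears. That is right, but immortal person-time takes its place. Neither reading is clean.

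A further reply is that one general rule, counting only first codes after entry, would also settle the cases covered by rules 1 and 3. That is true, and it favours making the correction once for all three groups.

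A reader might also infer that the Cox and Poisson analyses would use different case sets from Phase 1, or that the age strata would suffer most because in-study diagnoses fall mainly in children. The documents do not support either. Phase 2 states neither the time origin nor how the Poisson counts are built, so the first is only a possibility. The protocol gives no ages at diagnosis, so the second has no basis.

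**Conclusion.** The point holds as an inconsistency in the protocol's stated rules. For patients first coded with intellectual disability in the study, the start of follow-up, rule 2 and the second inclusion criterion cannot all be applied together, and a case can be indexed before follow-up begins. This is not detail left to an analysis plan: the protocol fixes all three, and a plan that followed them would inherit the conflict.

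If rule 2 is applied literally with person-time from the diagnosis, the incidence is biased upwards; that direction does not depend on the assumed inputs. The size does, entirely. About 5% to 17% applies if 10% to 30% of patients are first coded in the study and the behaviour rate is the same before and after the code. The range widens to about 2.5% to 31% if the earlier rate is half or double. It would be too strong to say that the protocol directs these events into the numerator. The correction should be made, because it touches the first research question and is cheap.

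**What to change.** In Definition of the study population:

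1. Define one cohort entry date per patient: the latest of 1/1/2009, the date the registration requirement is met, and the first intellectual-disability code.
2. Reword rule 2 so that a case is incident only if the first challenging-behaviour code falls after that entry date and before censoring.
3. Treat any patient with an earlier challenging-behaviour code as prevalent at entry: outside the risk set for the incidence and first-event Cox analyses, and reported separately as a count.
4. Reword the second inclusion criterion to: first intellectual-disability code during the study period, with at least six months' registration before that date.

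The cost is wording only. The dates needed are already in the planned extract. The downside is fewer counted cases and a somewhat lower incidence figure.

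### Cohort entry is defined inconsistently for patients who register after 1 January 2009 with intellectual disability already recorded, and prior challenging-behaviour diagnoses are not removed from the incidence risk set

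*Protocol*

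**What the plan says.** All the entry rules stand in one section of the Protocol, Definition of the study population.

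- Start of the cohort: "Earliest cohort entry date will be 1/1/2009".
- Start of follow-up: "Patients who register after 1/1/2009, or who are diagnosed with intellectual disabilities during the study period, will be followed from that date".
- First inclusion criterion: patients with intellectual disabilities must be "registered at a general practice for at least six months prior to cohort entry date".
- Second inclusion criterion: "patients who receive a diagnosis of intellectual disabilities after cohort entry date and have a valid registration status for at least six months".
- Index date of a case, first option: "1/1/2009 (if a patient is actively registered on this date with a diagnosis of challenging behaviours prior to 2009").
- Index date of a case, third option: "date of registration (if a patient's date of registration is after 1/1/2009 and they have a prior diagnosis to that registration"). The remaining option is the date of a first diagnosis made after 1/1/2009 while registered.

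The first research question, under Objectives, specific aims & rationale, asks: "What is the 1-, 5- and 10-year incidence of challenging behaviours". Phase 2 of the analysis uses Cox models, followed by a Poisson model for repeated events.

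**The concern.** Incidence and Cox analyses need one time zero per patient and a risk set of people who have not yet had the event. The section does not supply either without conflict.

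For a patient who arrives during the study with intellectual disability already on the record, one sentence starts follow-up on the day of registration, while a criterion asks for half a year of registration before entry. Two programmers working from this text could build different cohorts, with different denominators for the first research question.

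The index-date list adds a second, independent problem. It assigns a date to people whose challenging behaviour was diagnosed before they came under observation. If those people count as events, prevalence is reported as incidence.

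**Working it through.** **1. New registrants with intellectual disability already recorded.** Months of prior registration = entry date minus registration date. The follow-up sentence gives entry = registration date, so the result is 0 months against the 6 required, and the first criterion fails for every such patient. No sentence moves entry to registration plus six months. The third index-date option nevertheless assumes that new registrants are in the cohort. The same patients are therefore in by two rules and out by one.

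**2. Does another meaning of cohort entry help?** Suppose entry is 1/1/2009 for everyone. A person who registers later still lacks six months' registration at that practice before entry, so the conflict remains.

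**3. New registrants diagnosed with intellectual disability later.** They do not need the first criterion, because the second can admit them. Its six months can be read in two ways:

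| Reading | Consequence |
|---|---|
| Six months before the diagnosis | An ordinary look-back; no bias from the rule itself |
| Six months after the diagnosis | Patients who leave or die within six months are removed using later information, and the first six months of those kept are immortal time |

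The text does not choose between them.

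**4. Prior challenging-behaviour diagnoses.** A patient registered for years before 2009 meets the six-month rule in full. If diagnosed with challenging behaviour before 2009, that patient is indexed at 1/1/2009, which is day 0 of follow-up. A patient diagnosed before registering is indexed at registration, also day 0. The section gives no washout and no exclusion of prior cases. This problem therefore does not come from the six-month conflict, and resolving that conflict alone would leave it in place.

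**5. The Protocol's own counts.** 3,020,680 + 13,285,111 = 16,305,791; × 0.005 = 81,528.96, which reproduces 81,529. Then 81,529 × 0.165 = 13,452.3, which reproduces 13,452. Neither figure is disputed or directly changed by this point.

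**6. Illustration of step 4 only.** Let p be the share with a prior diagnosis and i the true 1-year incidence among the rest. If prior cases were counted at day 0, apparent 1-year incidence = p + (1 − p) × i. The values of i are assumed. The values of p are prevalences quoted in the Protocol: 16.5% from Sample size considerations, and 4% and 22% as the range in Study background. Using any of them as the share with a prior GP code is also an assumption.

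| p | i = 1% | i = 3% | i = 5% |
|---|---|---|---|
| 4% | 5.0% | 6.9% | 8.8% |
| 16.5% | 17.3% | 19.0% | 20.7% |
| 22% | 22.8% | 24.3% | 25.9% |

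For example, 0.165 + 0.835 × 0.01 = 0.173. The table shows why the treatment of prior cases matters; it is not an estimate of the bias.

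**The case against.** The best defence is that the Protocol never states that cohort entry and start of follow-up are the same date. If entry is 1/1/2009 or registration, and follow-up starts at a later intellectual-disability diagnosis, the second criterion's reference to a diagnosis after entry is coherent. That stands, so I do not claim a contradiction for newly diagnosed patients, only that the six months are not anchored. It does not rescue new registrants who already have the diagnosis (steps 1 and 2). Reading the first criterion's practice as any earlier practice would soften the conflict, but the Protocol neither says this nor says how earlier registration would be verified.

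Four stronger readings are tempting and are not supported:

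- *All new registrants are excluded.* Those first diagnosed with intellectual disability after registering can enter through the second criterion.
- *Most of the open cohort is lost.* The Protocol gives no registration turnover, so the share affected is unknown.
- *The second criterion creates immortal time.* That holds only if the six months follow the diagnosis. The first criterion looks back, so a look-back here is at least as natural.
- *Old diagnoses are certain to be counted as new events.* The list gives them an index date but does not say that they enter the incidence numerator. What is missing is a rule that keeps them out.

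It is also fair to say that 16.5% is an assumed point prevalence taken from a study of seven health authorities, not a rate of coded history. The Protocol's limitations section warns of under-recording, so using 16.5% in step 6 probably overstates the effect.

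**Conclusion.** The point holds in three parts.

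- For patients who register after 1/1/2009 with intellectual disability already recorded, the follow-up sentence and the index-date list conflict with the first inclusion criterion, and nothing elsewhere in the Protocol resolves it.
- The second criterion's six-month window is ambiguous, and one of its two readings conditions on the future.
- Independently, diagnoses of challenging behaviour made before observation are placed at day 0 with no rule to remove them, which does not fit an aim of estimating incidence.

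The first part rests on wording alone. Its size, and that of the other two, cannot be calculated from the Protocol: the number of new registrants, the rate at which old diagnoses are re-coded and the true incidence are all absent. The text should be corrected before the cohort is built, because the risk set for the 1-, 5- and 10-year incidence and for the first-event Cox models cannot be reproduced from it as it stands.

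**What to change.** Replace the entry rules with a single definition, and bring the index-date list into line with it:

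1. Cohort entry and start of follow-up are the latest of 1/1/2009, the registration date plus six months, and the date of the first intellectual-disability code.
2. Delete both six-month inclusion bullets and the sentence that follows patients from registration. The six months then always fall before entry.
3. Treat any challenging-behaviour code before entry, including in the first six months of registration, as prevalent. Exclude these patients from the incidence and first-event Cox risk set, and report their number separately.
4. Revise the index-date list so that an incident case is indexed only at a first code after entry. Without this step, the registration-date option would fall six months before entry, and codes from the first six months would still be indexed as new, so a new contradiction would replace the old one.

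The cost is Protocol wording and up to six months of person-time per new registrant. Patients with earlier challenging behaviour leave the first-event analyses but remain visible in the separate report. The Protocol's expected counts of 81,529 and 13,452 need no change as a direct result.
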